## Introduction

1

Stroke is a leading cause of mortality and long-term disability (1). Stroke can elicit a range of neurological deficits or handicaps, including speech and language problems. Dysarthria is a neurologic motor speech disorder caused by disruptions in the cranial nerve and muscular control of the speech mechanism. It is estimated that approximately 22–60% of stroke patients experience dysarthria within the first week following a stroke (2–4). Approximately 35% of patients continue to exhibit dysarthria even after 6 months (5). Moreover, post-stroke dysarthria significantly impairs speech intelligibility and articulation movements (2). This impairment leads to substantial communication difficulties, emotional distress, social isolation, and poor quality of life (6, 7).

Interventions for dysarthria involve a range of strategies, such as neurorehabilitation, behavioral exercises, and social support (2). Behavioral speech exercises strengthen the breathing and oral muscles to improve speech control. Strategies such as slowing down speech or controlling pitch are also used to enhance speech intelligibility. The treatment plan should be personalized based on the patient’s prior communication ability, recovery stage, and needs (8).

Despite the critical need for effective treatment of dysarthria, traditional therapies are often limited by their monotonous repeated nature. Consequently, these challenges can result in reduced treatment adherence (9). Moreover, the significant time and effort required by physicians and speech-language pathologists (SLPs), often restricts patient access to necessary therapeutic resources (10). Studies have indicated that only approximately one-third of patients receive adequate speech therapy, with substantial variations in therapy frequency (11). Given these limitations, personalized dysarthria treatment becomes necessary because of the diverse patterns of speech impairment in post-stroke dysarthria caused by different stroke lesions (12). These observations highlight the urgent need for alternative approaches, such as personalized digital speech therapy.

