### Randomization

2.3

Participants will be randomly allocated in a 1:1 ratio to either the intervention group or control group. An independent third-party entity will oversee the randomization process to ensure impartiality.

Additionally, the trial will stratify participants based on the onset period of their stroke: acute to subacute phase (within 1 month of onset) and chronic phase (from 1 month to 6 months of onset) (24). After confirming participants’ eligibility, we will assign each participant a sequential number for group allocation. For each stratum, we will actively allocate participants in a 1:1 ratio to either the intervention or the control group. A secure computerized system will generate an unpredictable and concealed allocation sequence. A blinded researcher will manage this sequence in opaque envelopes, which will be opened after the participant’s enrollment and baseline measurements are complete.

To ensure group balance and methodological rigor within each stratum, we will use permuted blocks of sizes two and four (25). The block size and allocation sequence details will remain confidential and inaccessible to the team members involved in recruitment, treatment, and assessment until the conclusion of the study.

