#### Control group

2.5.2

Participants allocated to the control group will undergo conventional therapy for post-stroke dysarthria over 4 weeks. In the absence of a standard protocol for post-stroke dysarthria treatment in South Korea, we have developed a conventional speech therapy workbook. This workbook integrates various clinically validated behavioral therapy techniques (2, 34). Its content is aligned with the intervention group’s digital speech therapy application to ensure consistency in treatment approaches. Participants will engage in the workbook for 60 min daily, 5 days a week, for 4 weeks to match the intervention group’s treatment dose and frequency. The workbook ensures treatment consistency across the multiple centers involved in this clinical trial. Before starting therapy, the researchers will guide the participants using the conventional therapy workbook.

In line with the intervention group, occasional guidance or support from family members will be allowed. This approach ensures that both groups have access to similar levels of support. By doing so, we promote equality in the treatment conditions across the groups. During regular follow-ups, researchers will monitor the extent and nature of any assistance family members provide. This monitoring will help ensure that the level of support remains balanced and appropriate for both groups.

Researchers will conduct daily follow ups to ensure adherence to conventional therapy workbook. During these interactions, researchers will discuss the participants’ progress, address challenges, and provide support and encouragement to maintain consistent participation in therapy. This approach ensures that the control group receives the same level of attention and support as the intervention group, thereby maintaining trial integrity. After the clinical trial, participants in the control group will also have access to the digital speech therapy application.

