### Outcome measurements

2.6

The study will span 4 weeks, and the details are provided in Table 2. Three assessment stages will be conducted during the process.

**Table 2 tab2:** Schedule of enrollment, interventions, and assessments.

	Enrollment	Randomization and allocation	Post-allocation		Close-out
Timepoint	Pre-baseline		Baseline	4 weeks	Post-study
Enrollment					
Eligibility screen	X				
Informed consent	X				
Allocation		X			
Interventions					
Conventional speech therapy					
Digital speech therapy application					
Assessment					
Speech intelligibility			X	X	
Percentage of consonants correct			X	X	
Oral diadochokinetic			X	X	
Maximum phonation time			X	X	
Depression			X	X	
Quality of life			X	X	
System usability					X

Demographic and clinical characteristics will be recorded after enrollment in the study. This initial recording includes demographic data (age and sex), medical history, stroke information (type and location of stroke and post-stroke duration), level of impairment measured using the NIHSS (23), cognitive status determined using the Korean Mini-Mental State Examination (K-MMSE) score (20), and Clinical Dementia Rating (CDR) tests (36). The demographic and clinical characteristics of the participants are shown in Table 3.

**Table 3 tab3:** Variables evaluated at baseline and study period.

Components	Subcategories
Age	Years
Gender	Male / Female
Medical history	Medication history, concomitant disease history (for example, dementia [Alzheimer’s disease, vascular dementia], central nervous system infection [e.g., human immunodeficiency virus, syphilis, Creutzfeldt-Jakob disease], Pick’s disease, Huntington’s disease, Parkinson’s disease, and others).
Medication	Details of concomitantly administered drugs (for example, medications for dementia treatment, central nervous system stimulants, anticholinergics, tricyclic antidepressants, typical antipsychotics, sleeping pills, typical antipsychotics, anxiolytics, antidepressants, and thyroid hormone)
Type of stroke	Ischemic/hemorrhagic
Stroke lesion location	Cortical (for example, frontal, parietal, and so on), subcortical, cerebellum, thalamus, basal ganglia, and so on.
Side of stroke involvement	Left/Right
Time to enroll after stroke	In days
Cognitive function	Korean Mini-Mental State Exam, Clinical Dementia Rating
Neurological status	National Institute of Health Stroke Scale
Visual function	Intact/Non-intact
Hearing function	Intact/Non-intact
Aphasia	Yes/No

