### Analysis

2.7

The primary objective of this trial is to investigate the non-inferiority of the intervention group compared to the control group in terms of changes in speech intelligibility from baseline to post-treatment. The hypothesis is as follows:

$$H_{0}:\mu_{t}-\mu_{c}<\delta \;vs\;H_{1}:\mu_{t}-\mu_{c}\geq \delta$$

Where *μt* is the mean change in speech intelligibility score in the intervention group using the digital speech therapy application, and *μc* is the mean change in the control group receiving conventional speech therapy. It is assumed that there is no difference between the two groups, and this study seeks to establish the non-inferiority of the groups. The non-inferiority margin *δ* is set at 19 points, based on the assumption that a difference of 1 to 19 points on the speech intelligibility scale is clinically non-inferior (45).

The sample size required for the non-inferiority trial was determined using a statistical formula (46). This involved setting the significance level (alpha) to 0.025 for a one-sided test and targeting a power of 80% (*β* = 0.2) (47) with a standard deviation of 24.9 (48). This calculation revealed that 28 participants are required for each group. A total of 56 participants are required for the trial. To account for a possible dropout rate of 30%, we aim to recruit a total of 76 participants, with 38 participants in each group.

$$n=\frac{2{\left(z_{\alpha }+z_{\beta }\right)}^{2}\sigma^{2}}{{\left(\mu_{t}-\mu_{c}-\delta \right)}^{2}}\approx 28$$

Analyses will be performed using SPSS software (version 27; IBM Corp., Armonk, New York). Descriptive statistics will summarize the demographic data and outcome measures. For interval estimates, 95% confidence intervals will be provided. An intention-to-treat (ITT) analysis will include all randomized participants. Additionally, we will conduct a per-protocol (PP) analysis which includes only participants who fully adhered to the intended protocol.

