First, the Shapiro–Wilk test will assess of the normality of the distributions. Based on these results, the appropriate parametric (independent two-sample t-test) or non-parametric test (Mann–Whitney U test) will be chosen for between-group comparisons. Then, mixed repeated-measures analysis of variance (ANOVA) will evaluate the changes over time within subjects and between groups, with fixed effects for time, group, and their interactions. Mauchly’s test will check sphericity by applying the Greenhouse–Geisser, if necessary. For significant findings, Tukey’s HSD tests will conduct post-hoc analyses with Bonferroni correction to control for the overall type I error rate at 0.05. The benchmark for statistical significance is set at *p* < 0.05.

We will address missing data using multiple imputation techniques and the Last Observation Carried Forward (LOCF) method. This approach aims to minimize bias and ensure the robustness of efficacy outcomes (49). Subgroup and sensitivity analyses will be conducted to explore the effects of participant characteristics and institutional factors on the primary efficacy results. In addition to the primary analysis, we will conduct subgroup analyses to examine the efficacy of our digital speech therapy application in various settings. Subgroup analyses include comparing its use during hospitalization with post-discharge home use. These analyses aim to provide a deeper understanding of how the setting influences the effectiveness of the therapy.

Furthermore, additional subgroup analyses will focus on the effects of the interventions across different stroke phases. Since participants are stratified based on the onset period of their stroke into acute to subacute, and chronic phases, these subgroup analyses will explore how the efficacy of the intervention varies between these two distinct stroke phases. We will perform regression analyses within each group stratified by the stroke onset period. If the statistical analysis reveals significant mean differences between various groups, post-hoc tests will be conducted to identify the specific groups among which these differences exist. This approach will provide valuable insights into whether the timing of a post-stroke intervention influences the efficacy of digital speech therapy. No interim analyses are planned to maintain the integrity of the non-inferiority margin or control for type I error rate.

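### The hospital-versus-home subgroup analysis is, as worded, a non-randomised contrast within the app arm, and Table 3 lists neither setting nor outside speech therapy to help interpret it

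*Protocol article*

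**What the plan says.** Section 2.7 (Analysis) of the protocol article defines the primary result as the between-arm difference in mean change in speech intelligibility. The non-inferiority margin "is set at 19 points, based on the assumption that a difference of 1 to 19 points on the speech intelligibility scale is clinically non-inferior". Beyond that result, the section plans to look at the app's efficacy by setting: "Subgroup analyses include comparing its use during hospitalization with post-discharge home use". The pronoun refers to the application. The stated purpose is to learn how setting bears on effectiveness. The section does not say whether the workbook arm enters this comparison, or at what moment a participant's setting is fixed.

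On other treatment, the article is specific in places. Table 1 excludes interfering concomitant medication. Table 3, which lists the variables evaluated at baseline and during the study, includes "Details of concomitantly administered drugs". Sections 2.5.1 and 2.5.2 have researchers follow family assistance in both arms. Speech therapy from outside the trial appears in none of these places, and Table 3 has no row for inpatient or home status. It does list days from stroke to enrolment.

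Section 2.3 enrols patients within 1 month of stroke (one stratum) and from 1 to 6 months (the other). The Discussion acknowledges that dysarthria is treated in hospital. The Introduction says that "only approximately one-third of patients receive adequate speech therapy, with substantial variations in therapy frequency".

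**The concern.** Patients still in hospital and patients already at home differ in more than their surroundings. Those in hospital are likely to be earlier after stroke, when spontaneous recovery is faster, and may be receiving ward speech therapy as well. A comparison confined to app users attributes all of this to setting.

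Discharge adds a second difficulty. A participant discharged in week 2 uses the app in both places, and early discharge may itself follow good recovery. If setting is classified by what happens after randomisation, the grouping can depend on the course of the illness.

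At stake is a published statement about where the app works better, which readers may use to decide where to deploy it. The article tracks drugs and family help but does not list the co-intervention closest to the primary outcome. On the data it describes, nobody could later check whether an apparent setting effect was a therapy effect.

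**Working it through.** **1. The plan's own figure.** Inputs from section 2.7: margin 19, SD 24.9, "It is assumed that there is no difference between the two groups", and "setting the significance level (alpha) to 0.025 for a one-sided test and targeting a power of 80" per cent.

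n = 2 × (1.960 + 0.842)² × 24.9² / 19² = 26.96, so 27 per arm by the normal formula. The t-based calculation gives 28 (power 0.801). The stated 28 per arm is reproduced. The same SD is used below, with 28 per arm (the calculated size) and 38 per arm (the recruitment target).

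**2. What the literal contrast estimates.** Mean change among app users in hospital minus mean change among app users at home equals s + r + t, where
- s is any effect of setting,
- r is the difference in spontaneous recovery,
- t is the difference due to non-trial speech therapy.

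Stroke phase and days since stroke are recorded, so r can be partly adjusted for. Nothing listed in Table 3 bears on t. Setting itself must be collected somewhere if the analysis is to be run, but it is not listed either.

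**3. Precision of the within-app contrast (even split assumed).**
- 28 in the arm: SE = 24.9 × √(1/14 + 1/14) = 9.41; 95% half-width = 1.96 × 9.41 = 18.4 points.
- 38 in the arm: SE = 24.9 × √(1/19 + 1/19) = 8.08; half-width 15.8 points.

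Suppose there is no setting effect (s = 0) and the other causes add d = r + t points. The chance of a nominally significant result at the two-sided 5% level is Φ(d/SE − 1.96) + Φ(−d/SE − 1.96):

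| Assumed d | 28 in arm | 38 in arm |
|---|---|---|
| 5 | 8% | 10% |
| 10 | 19% | 24% |
| 15 | 36% | 46% |

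The article gives no value for d; the range is illustrative. The bias is d itself, whatever the p-value.

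**4. The between-arm alternative.** Take (app − workbook) in hospital minus (app − workbook) at home. Any r or t that is the same in both arms cancels within each setting. The cost is precision, because four cell means now enter:
- 28 per arm, 14 per cell: SE = 24.9 × √(4/14) = 13.3; half-width 26.1 points.
- 38 per arm, 19 per cell: SE = 24.9 × √(4/19) = 11.4; half-width 22.4 points.

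Both half-widths exceed the 19-point margin. The interaction can be described, but it cannot support a firm claim.

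**5. Timing.** Randomisation protects a subgroup contrast only if the subgroup is fixed beforehand. Setting at randomisation meets that condition; setting during the four weeks does not.

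**The case against.** **Silence in a condensed article.** The full protocol may record outside therapy and setting, and what the planned follow-up contacts capture is not shown. This stands as a limit: the article does not list these items, which is not proof that they go uncollected. It still gives its restricted drugs, recorded variables and monitored family help in some detail, so the question is fair.

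**A between-arm reading is possible.** The setting analyses sit beside subgroup analyses of the primary result, which is a between-arm difference. On that reading, therapy common to both arms cancels. The wording points to the app's own use, however, and nothing in the section resolves the ambiguity. Stroke phase has its own planned subgroup analysis, but that does not adjust the setting contrast.

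**Stronger inferences a reader might draw.** One is that therapy received by both arms hides a true deficit and inflates the false non-inferiority rate. The document does not support this, for three reasons:
- "Participants will be randomly allocated in a 1:1 ratio to either the intervention group or control group", within strata by stroke phase, so outside therapy is balanced in expectation. An equal additive gain leaves the difference unchanged. Convergence requires that outside therapy substitutes for trial therapy, that scores reach a ceiling, or that use is unequal.
- The hypothesis concerns the mean changes actually obtained. If background care closed a 19-point deficit in one third of app users, the mean deficit would be 19 × 2/3 = 12.7 points. That is inside the margin, so concluding non-inferiority would not be a type I error under the stated hypothesis.
- The Introduction's one-third describes access to adequate therapy in general, not concurrent therapy among trial participants.

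A reader might also see a contradiction in the workbook schedule being set "to match the intervention group’s treatment dose and frequency". That sentence matches time on the two trial materials and says nothing about total therapy received.

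**Conclusion.** The point holds for the setting analysis. As worded, it is a non-randomised within-arm comparison whose result would be read as an effect of setting. Time since stroke, recovery and in-hospital therapy are plausible rival explanations, and setting may change after randomisation. The size of the distortion cannot be derived from the article. Under the assumed 5 to 15 points from other causes, a spurious significant finding has a probability of roughly 8% to 46%, depending on the number in the arm, instead of 5%.

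This rests on the literal reading of the sentence, an even split by setting, and SD 24.9 applying in both settings. It concerns a secondary analysis. It gives no ground for saying that the primary conclusion is biased. Recording outside therapy is worthwhile because it would show whether the arms were balanced, not because imbalance has been shown.

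**What to change.** 1. **Setting.** Define it as inpatient or home at randomisation and add it to Table 3. Replace the within-app contrast with the between-arm difference in each setting and the arm-by-setting interaction, using both arms and with stroke phase in the model. Label it exploratory, state the expected half-width (about 26 points with 28 per arm and an even split), and describe the result as an association, since setting is still not randomised.
2. **Outside speech therapy.** Record type and minutes per week in both arms at the follow-up contacts already planned, and report them by arm.
3. **Use of that record.** Any analysis restricted by therapy received after randomisation should be supportive only. Making it a per-protocol exclusion that drives the conclusion would invite selection bias, for example if poor responders in one arm seek more therapy.

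The cost is one or two form items, a few minutes per contact and a reworded paragraph. The interaction estimate will be imprecise. The therapy record has to be kept prospectively, because it would be hard to reconstruct afterwards.

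### The planned phase subgroup analysis (regressions within groups, then post-hoc tests) does not test whether the app's effect differs between stroke phases and can easily suggest a difference where none exists

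*Protocol article*

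**What the plan says.** Section 2.3 (Randomization) defines two strata by time since stroke, within 1 month and from 1 to 6 months, and fixes the ratio inside each: "For each stratum, we will actively allocate participants in a 1:1 ratio to either the intervention or the control group".

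Section 2.7 (Analysis) poses the subgroup question: "these subgroup analyses will explore how the efficacy of the intervention varies between these two distinct stroke phases". The method follows: "We will perform regression analyses within each group stratified by the stroke onset period". A second step is conditional: "If the statistical analysis reveals significant mean differences between various groups, post-hoc tests will be conducted to identify the specific groups". The section expects the result to show "whether the timing of a post-stroke intervention influences the efficacy of digital speech therapy".

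The only interaction named in the analysis belongs to the mixed ANOVA, "with fixed effects for time, group, and their interactions". Phase is not a factor in that model, and no arm-by-phase term appears anywhere in the article.

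A further subgroup concerns setting: "Subgroup analyses include comparing its use during hospitalization with post-discharge home use".

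**The concern.** Whether efficacy varies by phase is a question about a difference of differences: app minus workbook in early patients, against app minus workbook in later patients. The stated method does not estimate that quantity. The phrase about regressions within each group has two readings.

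- **Within each arm.** The regression compares earlier with later patients on the same therapy. Its phase coefficient contains whatever recovery separates the phases, plus any difference in treatment effect. With no comparison between arms, the two cannot be separated.
- **Within each phase.** This gives two separate arm comparisons. One significant and one non-significant result is not evidence that the two effects differ.

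The post-hoc step does not repair either reading. It looks for groups with different means, and a recovery difference shared by both arms is enough to trigger it.

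The setting subgroup has a related weakness. Discharge can fall inside the 4 weeks of treatment. If setting is classified by where the patient was treated during that time, it is a post-randomisation state and the comparison loses the protection of randomisation.

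The Discussion presents stratification by phase as filling a research gap, and the Abstract hopes to provide a foundation for larger trials. A spurious phase finding could misdirect their design.

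**Working it through.** **Inputs from section 2.7.** SD 24.9; margin 19 points; one-sided alpha 0.025 for non-inferiority; 0.05 for other tests; true difference assumed 0; 28 per group (56) evaluable; 76 to be recruited.

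**Assumptions not in the article.** An even phase split, giving 14 per arm per phase at N = 56 and 19 at N = 76; true effects of 10 and 15 points, equal in both phases; a recovery difference between phases of 10 to 20 points, shared by both arms.

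**Step 1, the plan's own figure.** n = 2 × (1.960 + 0.842)² × 24.9² / 19² = 26.96, so 27 per group. The noncentral-t calculation gives 28, as stated. The inputs therefore reproduce the plan's evaluable size.

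**Step 2, precision.** The half-width of the 95% CI in one phase is t × SD × √(2/n). For the difference between phases it is t × SD × √(4/n), with n the number per arm per phase.

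- N = 56, one phase: 2.056 × 24.9 × √(2/14) = 19.3 points.
- N = 56, difference: 2.007 × 24.9 × √(4/14) = 26.7 points.
- N = 76, one phase: 2.028 × 24.9 × √(2/19) = 16.4 points.
- N = 76, difference: 1.993 × 24.9 × √(4/19) = 22.8 points.

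**Step 3, reading within phase.** The phases contain different patients, so if each has probability p of a significant result, they disagree with probability 2p(1 − p). The true effect is the same in both phases throughout.

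| True effect | Criterion | N = 56: p, disagreement | N = 76: p, disagreement |
|---|---|---|---|
| 0 | superiority, two-sided 0.05 | 0.050, 9.5% | 0.050, 9.5% |
| 10 | superiority | 0.176, 29% | 0.226, 35% |
| 15 | superiority | 0.336, 45% | 0.439, 49% |
| 0 | meets the 19-point margin | 0.49, 50% | 0.63, 47% |

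Simulation (40,000 runs per scenario), run for true effects of 0 and 10 points, agrees. With a 70:30 split at a true effect of 10, superiority disagreement is 30% (N = 56) and 36% (N = 76). At a true effect of 0, disagreement on the margin is about 56% and 55%.

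**Step 4, reading within arm.** There is no effect modification, but earlier patients recover 10, 15 or 20 points more in both arms. With an even split, phase is then significant in the app arm in 18%, 34% and 54% of trials at N = 56, and in 23%, 44% and 67% at N = 76.

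**Step 5, trigger for the post-hoc tests.** Take an omnibus F test of the four arm-by-phase means, with noncentrality N × (d/2)² / SD² for a shared phase difference d. For d = 15 and N = 56 this is 56 × 7.5² / 24.9² = 5.08 on 3 and 52 degrees of freedom, and the power is 42%. For d = 10, 15 and 20 the test is significant in 20%, 42% and 68% of trials at N = 56, and in 27%, 56% and 83% at N = 76, although the treatment effect does not vary by phase.

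**Step 6, the alternative.** In the same simulations the arm × phase test rejects in 4.8% to 5.2% of trials in every scenario.

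**The case against.** The best defence is that the sentence is ambiguous and condensed, that model terms are often left to an analysis plan, and that the article promises 95% confidence intervals and calls these additional subgroup analyses that will explore. It never says that a significant phase will be set against a non-significant one. All of that is fair. But the article does more than stay silent: it names a method and says what it will show, and on neither reading does the method show it.

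A reader might infer several stronger things that the article does not support.

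- *The analysis is bound to report false phase differences.* It is not. At the protocol's own assumption of no treatment difference, superiority disagreement is only about 10%. The 29% to 49% figures need non-zero effects that the protocol does not assume. The margin figures of 47% to 50% do hold at zero difference.
- *A within-arm regression measures only spontaneous recovery.* The coefficient mixes recovery with treatment effect. If both arms are fitted, the difference between their phase coefficients is the interaction estimate. What is missing is any stated plan to make that comparison.
- *Post-hoc tests are empty with two arms and two phases.* Two by two gives four cells, so pairwise tests have content. They do not isolate the interaction.
- *Hospital or home setting is tied to stroke phase.* That is plausible, but the article does not say so. Nor does it say when setting is classified.
- *The trial's main conclusion is at risk.* Section 2.7 makes non-inferiority on intelligibility the primary objective, and that does not depend on this subgroup.

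It is also true that the remedy gains little precision. With an even split and normal approximation, the interaction detectable with 80% power is 37.3 points at N = 56 and 32.0 at N = 76.

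**Conclusion.** The point stands as a fault in an exploratory analysis that should be corrected. The stated method does not test whether the treatment effect differs between phases, and it can easily produce an apparent difference when there is none. On the phase-by-phase reading, disagreement runs from about 10% to 50% of trials, depending on the true effect, the criterion and the number analysed. A direct interaction test would err in about 5%. These rates rest on an assumed even phase split, equal true effects in both phases and the protocol's SD of 24.9. The within-arm and post-hoc rates also rest on an assumed shared recovery difference of 10 to 20 points. The logical fault depends on none of these numbers. For the setting subgroup the concern is conditional: it applies if setting is classified after randomisation, and no size can be put on it from the article.

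**What to change.** Replace the within-group regressions and the post-hoc tests with one model on all randomised patients for change in intelligibility, with arm, phase, arm × phase and baseline intelligibility as terms. Report the interaction estimate with its 95% CI and the arm difference with its CI in each phase. Label all of this exploratory, and state that no conclusion about timing will be drawn from separate significance results. The article names no baseline-adjusted model for the primary comparison, so this model should be written out in full.

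For the hospital versus home subgroup, classify setting at randomisation and use an arm × setting term in the same way.

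The cost is wording plus one baseline field for setting, which Table 3 does not list. Phase is already the stratification factor and baseline intelligibility is already measured. No extra patients are needed. The downside is that the interval for the interaction will be about ±23 to ±27 points, so the analysis will prevent a misleading claim but will probably leave the timing question open.
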